### Ethical Considerations

Ethics approval for this study will be obtained from the Yale University Human Research Protection Program prior to initiation. The protocol will be registered on ClinicalTrials.gov, and the registration record will be maintained and updated throughout the study to reflect any amendments or changes in status. The approved protocol version number and date will be displayed on all study documents, including the analysis plan, and any site-specific requirements mandated by participating clinics will be honored to ensure compliance with local governance standards.

This study will be conducted across multiple academic centers under a coordinated governance framework. Each participating site will obtain local institutional review board approval or reliance agreements as appropriate. Data sharing arrangements will be governed by formal data use agreements between institutions, ensuring compliance with HIPAA and applicable federal and institutional privacy regulations. All shared datasets will be deidentified prior to transfer and stored in secure, access-controlled environments. All participants will provide written informed consent prior to participation.

A central study steering committee comprising investigators with expertise in hepatology, data science, and implementation science will oversee study conduct, protocol adherence, and data integrity. Algorithm development and validation will be conducted within secure computing environments with version control and audit trails.

During the implementation phase, oversight of the CDS tool will include monitoring for safety, usability, and unintended consequences. Because the CDS tool is intended to support, not replace, clinician decision-making, final clinical decisions will remain at the discretion of the treating clinician. Any unexpected system behavior, performance concerns, or workflow disruptions identified during simulation or pilot deployment will be documented and reviewed by the study team, with predefined procedures for modification or suspension of the tool if necessary.

Any protocol amendments that materially affect eligibility criteria, study outcomes, data collection procedures, statistical analysis methods, consent language, or confidentiality protections will be submitted to the institutional review board for review and approval before implementation. The study team will maintain a comprehensive version history documenting the rationale for each change, along with dates and approvals. When amendments alter information that participants relied upon to provide informed consent, the research team will reconsent all active participants using revised documents. Substantive amendments will also be reflected in the ClinicalTrials.gov record and communicated to site leaders and stakeholders involved in recruitment and oversight.

This protocol has been developed in accordance with the SPIRIT (Standard Protocol Items: Recommendations for Interventional Trials) guidelines (Checklist 1) [28]. A SPIRIT figure outlining the schedule of enrollment, interventions, and assessments is available in Checklist 1. Upon completion, study findings will be disseminated through peer-reviewed publications, presentations at national and international conferences, and summaries shared with participating sites. The final dataset, stripped of identifiers, will be made available through controlled-access repositories under appropriate data sharing agreements to promote reproducibility and secondary analyses. Results will be reported regardless of outcome, and any deviations from the original protocol will be clearly documented and justified in the final manuscript. Additionally, the ClinicalTrials.gov record will be updated with summary results in compliance with federal requirements.

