### Eligibility Criteria

Adults aged 18 years or older with a confirmed diagnosis of PBC according to American Association for the Study of Liver Diseases criteria (ie, defined as elevated ALP of ≥1.5 times the upper limit of normal in combination with a positive antimitochondrial antibody or disease-specific antinuclear antibodies such as sp100 or gp210) [2]. For individuals who are seronegative, histological confirmation through liver biopsy will be mandatory. All participants must have been receiving standard therapeutic dosing of ursodeoxycholic acid for a minimum of 3 months prior to enrollment, defined as 13 to 15 mg per kilogram of body weight per day administered in 2 or 3 divided doses [2]. Patients who are on second-line therapies, including farnesoid X receptor agonists or peroxisome proliferator–activated receptor agonists, will also be eligible, and therapy class will be recorded as a covariate. Additionally, baseline elastography data, including LSM and SSM, must be available within 6 months of enrollment.

Individuals will be excluded if they have previously undergone liver transplantation or are currently listed for transplantation or if they present with decompensated cirrhosis at baseline, defined as Child-Pugh class B or C [16]. Other exclusion criteria include active malignancy, uncontrolled systemic illness, pregnancy, or inability to provide informed consent. Patients with significant alcohol consumption within 6 months of enrollment (ie, more than 20 grams per day for female individuals or more than 30 grams per day for male individuals or an Alcohol Use Disorders Identification Test–Consumption score of 4 or higher) [17] will not be eligible. Additional exclusions are coexisting chronic liver diseases such as chronic viral hepatitis, hemochromatosis, Wilson disease, or alpha-1 antitrypsin deficiency, as well as active or suspected drug-induced liver injury within the prior 6 months, including drug-induced autoimmune hepatitis (AIH). Any condition deemed by the investigators to compromise participant safety or data integrity will also result in exclusion. A summary of inclusion and exclusion criteria is provided in Textbox 1.

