### Harms

This pilot implementation component is considered minimal risk for multiple reasons. First, the randomized crossover simulation will involve standardized simulated or deidentified patient cases rather than live clinical encounters. The participants in this simulation component will be health care providers who interact with an EHR interface in a controlled environment. The decision support tool will provide risk estimates and triage recommendations based on synthetic or deidentified data. As such, the simulation component is not expected to pose physical harm, diagnostic error affecting patient care, or adverse clinical outcomes. For the observational/model-development components, adults with PBC will contribute clinical, elastography, and patient-reported outcome data under institutional review board–approved procedures and standard privacy protections.

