### Participant Timeline

Participants will enter the study and begin with baseline assessments, which include collection of demographic information, medical history, and initial laboratory values, as well as elastography measurements for liver and spleen stiffness. At this visit, participants will also be enrolled in the PRO system, with instructions for completing the WI-NRS and the PBC-40 questionnaires. These assessments will continue throughout the observation period to capture longitudinal symptom trajectories. The schedule of enrollment, interventions, and assessments is provided in Checklist 1.

Biochemical data will be collected at monthly intervals for the duration of the study, ensuring high-resolution monitoring of disease activity. Elastography will be repeated at predefined intervals, typically every 6 to 12 months or as clinically indicated, to track changes in liver and spleen stiffness over time. Clinical outcomes such as the development of varices, ascites, or hepatic encephalopathy will be monitored continuously through routine clinical care and documented in the study database.

For participants involved in the implementation phase, the timeline includes a randomized crossover simulation in which clinicians will manage deidentified cases under 2 conditions: usual care and CDS-assisted care. This simulation will occur after the development and validation phases are complete. Following the simulation, a pragmatic pilot will be conducted in real-world hepatology clinics, where the CDS tool will be integrated into the EHR and used during routine visits. Clinician usability and trust assessments will be administered at the end of each simulation period and again after the pilot phase.

The overall duration of participation for patients in the observational component is expected to be up to 24 months. Clinicians participating in the implementation evaluation will engage in shorter, structured sessions for simulation and a limited rollout period for the pilot.

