### Sample Size and Power Considerations

Because this protocol involves model development, validation, and implementation feasibility, the planned sample size was based on expected cohort availability and anticipated outcome events rather than a conventional hypothesis-testing formula. The sample size determination for this study is primarily driven by the second aim, which focuses on validating the predictive model for CSPH. On the basis of preliminary data and published estimates, we anticipate enrolling approximately 600 patients with PBC across participating sites [7]. This cohort size reflects the expected availability of retrospective and prospective data within the study time frame and ensures adequate representation of key subgroups, including patients with AIH overlap and MASH [19,20].

On the basis of prior PBC cohorts, the prevalence of portal hypertension or CSPH in hepatology referral populations has been reported to range from approximately 24% to 47% depending on disease stage and case mix [25,26]. With a projected sample of 600 participants, this corresponds to an estimated 144 to 282 CSPH events, which provides a sufficient number of outcome events to support model development and validation and evaluate improvements in model discrimination relative to established criteria such as Baveno VII.

In addition, sample size considerations accounted for model complexity. Current methodological guidance for prediction modeling recommends ensuring an adequate number of outcome events relative to the number of predictor parameters to reduce the risk of model overfitting. The anticipated event counts in this cohort are expected to support the planned set of candidate predictors while maintaining an appropriate events-per-predictor ratio for stable model estimation [27].

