### Data Collection

Retrospective data will be sourced from institutional EHRs and data warehouses, capturing historical laboratory values, elastography reports, and clinical outcomes relevant to PBC. Prospective data collection will be conducted in outpatient hepatology clinics using secure, HIPAA (Health Insurance Portability and Accountability Act)-compliant platforms such as REDCap for PROs. These outcomes will include validated instruments such as the WI-NRS, administered twice daily to capture circadian variation in pruritus, and the PBC-40 questionnaire, administered monthly to assess quality of life domains.

Biochemical data, including ALP, bilirubin, aminotransferases, albumin, and platelet count, will be collected at monthly intervals to provide high-resolution longitudinal trajectories. LSM and SSM values will be obtained at baseline and during scheduled follow-up visits, with probe frequency and stiffness values recorded in kilopascals to ensure standardization. Clinical outcomes such as time to variceal development, ascites, and hepatic encephalopathy will be tracked over a 24-month observation period.

All data will be deidentified prior to analysis and stored in secure environments that comply with institutional and federal privacy regulations. Quality control procedures will include automated range checks for laboratory values, standardized reporting templates for elastography, and audit trails for PRO completion. Missing data will be addressed using multiple imputation techniques to minimize bias and preserve statistical power. Data integration will occur through structured pipelines that normalize heterogeneous inputs for use in machine learning models, ensuring consistency across biochemical, imaging, and symptom domains.

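### The consent rule for all participants and the single enrolment-anchored criteria list also cover the retrospective patients, so part of the Aim 2 development data is selected on having avoided the severest outcomes

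*Protocol article*

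**What the plan says.** Five places in the protocol article bear on who can enter.

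- **Consent (Ethical Considerations).** "All participants will provide written informed consent prior to participation". No exception or waiver is mentioned.
- **Eligibility (Eligibility Criteria and Textbox 1).** One list serves the whole study. It excludes people if "they have previously undergone liver transplantation or are currently listed for transplantation", those with "decompensated cirrhosis at baseline, defined as Child-Pugh class B or C", and those with "active malignancy, uncontrolled systemic illness, pregnancy, or inability to provide informed consent". Liver and spleen stiffness must be available within 6 months of enrolment.
- **Baseline (Participant Timeline).** "Participants will enter the study and begin with baseline assessments". Baseline is therefore study entry, and no other time zero is given for patients known only from records.
- **Source of the data (Data Collection; Sample Size and Power Considerations).** "Retrospective data will be sourced from institutional EHRs and data warehouses, capturing historical laboratory values, elastography reports, and clinical outcomes relevant to PBC". On the 600: "This cohort size reflects the expected availability of retrospective and prospective data within the study time frame". The split between the two sources is not stated.
- **Phases (Table 1).** Phase 1 is a retrospective analysis for model development, and the patients in those records stand in the Participants column. The disease names in that table do not all fit a PBC study. I rely only on its structure.

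**The concern.** Aim 2 is to predict CSPH and early complications such as variceal bleeding and ascites. Historical records are valuable for this because their outcomes have already occurred, including the worst ones. The stated rules work against that. Someone with qualifying elastography several years ago who has since died cannot sign a form. If enrolment means today, someone since transplanted, placed on the list, or moved to Child-Pugh B or C is also out.

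Entry would then depend on what happened after the predictors were measured, which is selection on the outcome. It tends to remove the high-risk patients who went on to severe events. The observed event rate can fall, the relation between stiffness and outcome can weaken, and both calibration and AUROC, which are Aim 2 measures, can be distorted. A held-out split of the same cohort carries the same selection and would not show it. The Limitations section does not mention it.

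**Working it through.** **1. Does the consent rule reach retrospective patients?**

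- The rule covers all participants. Table 1 lists the patients in the retrospective records under Participants, and Sample Size and Power Considerations counts retrospective data towards the 600 to be enrolled.
- Textbox 1 repeats the consent condition as an exclusion, without separating the two components.
- The Harms section says that "adults with PBC will contribute clinical, elastography, and patient-reported outcome data under institutional review board–approved procedures and standard privacy protections". This names no waiver and does not limit the consent sentence.

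On the literal text, the rule applies to them.

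**2. Who is lost under each reading of enrolment?**

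| Reading | Died before consent | Transplanted, listed or Child-Pugh B/C since the historical scan |
|---|---|---|
| Criteria tested at present-day enrolment | excluded | excluded |
| Criteria tested at historical cohort entry | still excluded by the consent rule | not excluded by these criteria |

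The loss of patients who died holds under both readings. The other losses need the first.

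**3. Who is not lost?** CSPH itself is not an exclusion. The decompensation criterion is Child-Pugh class at baseline, so a past complication in a patient now in class A does not exclude. Varices, ascites and encephalopathy are tracked for 24 months after entry.

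**4. The plan's own figure.** 600 × 0.24 = 144 and 600 × 0.47 = 282. The stated 144 to 282 events reproduce.

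**5. Illustration of size.** The documents give neither the retrospective share nor any loss rate, so all losses here are assumptions. Let p be the CSPH prevalence, L the share of CSPH patients lost before entry, and 10% the share of other patients lost. Suppose the whole cohort is retrospective and 600 are still enrolled.

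Observed share = p(1 − L) / [p(1 − L) + (1 − p)(0.90)]

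With L = 0.40:

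- p = 0.24: 0.144 / (0.144 + 0.684) = 0.174. Events: 600 × 0.174 ≈ 104, which is 40 fewer than 144.
- p = 0.47: 0.282 / (0.282 + 0.477) = 0.372. Events: 600 × 0.372 ≈ 223, which is 59 fewer than 282.

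| L | Share when p = 24% | Share when p = 47% |
|---|---|---|
| 20% | 21.9% | 44.1% |
| 40% | 17.4% | 37.2% |
| 60% | 12.3% | 28.3% |

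If half the cohort were retrospective, the shortfalls at L = 0.40 would halve to about 20 and 30.

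**6. Illustration for AUROC.** A binormal model was simulated with a true AUROC of 0.85, the value the Results section expects. A share q of CSPH patients was removed, concentrated at the highest risk scores, and no others were lost. The lower value in each range removes strictly the top-scoring cases; the upper removes cases with a probability that rises with the score.

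| q | Measured AUROC |
|---|---|
| 10% | 0.83 to 0.84 |
| 30% | 0.79 to 0.81 |
| 40% | 0.76 to 0.79 |

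The fall comes from losing the highest-scoring cases. Losses unrelated to the score would leave AUROC unchanged.

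**The case against.** The best reply is that the article never says consent is sought for historical records. The consent sentence is generic, the Harms section refers to board-approved procedures without naming individual consent, and approval is still to come. A waiver and an index date might stand in the full protocol or the ethics application, which are not shown. The elastography window also matters: if enrolment means today, an old scan alone qualifies nobody. Then either enrolment is contemporary, with recent scans and outcomes that follow, or it is historical cohort entry, with criteria applied at that date.

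Part of this stands. The sponsor may well intend a waiver, and the index date problem is partly inferred from silence. But neither reading clears the text. Contemporary enrolment leaves no true retrospective development cohort of the kind Table 1 describes. Historical entry still meets a consent rule without exceptions. The point is a stated rule that does not fit the design, not merely an omitted detail.

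A reader might infer more than the documents support:

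- **That the cohort holds only survivors, or that everyone with a complication is excluded.** Step 3 of the working shows otherwise. Excluding decompensation at time zero is also ordinary when incident complications are predicted; what matters is where time zero lies.
- **That 58 of 144 or 113 of 282 events would be lost** (0.40 × 144 and 0.40 × 282). Those are gross removals from an all-retrospective cohort with nobody replaced. The plan enrols about 600 regardless, so the net shortfall under the same assumptions is 40 and 59.
- **That Aim 2 cannot be answered, or that the model is bound to under-predict.** Prospective data also contribute, validation at a separate site is planned where feasible, and recalibration is foreseen if calibration proves poor in deployment. The direction of the bias is plausible; its extent is unknown.
- **That this is immortal-time bias.** No exposure time is misclassified. It is selection at entry.

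**Conclusion.** The concern holds in a limited form. As written, the consent rule, the consent-ability exclusion and the single enrolment-anchored list cover the retrospective patients. Those who died before consent cannot enter under either reading of enrolment. Those since transplanted, listed or now Child-Pugh B or C are also lost if eligibility is tested at present-day enrolment. The retrospective part of the Aim 2 development data is then selected on having avoided the severest outcomes, which can lower observed risk and distort calibration and AUROC.

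The size of the bias cannot be derived from the document. The calculated shares, event counts and AUROC values show what the mechanism could do under assumed losses. They are not estimates for this study.

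**What to change.** **Ethical Considerations and Textbox 1.** Limit written consent, and the exclusion for inability to give it, to prospective patients and clinicians. Request an ethics board waiver for the deidentified retrospective records.

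**Eligibility Criteria and Data Collection.** Define a historical index date for retrospective patients, for example the first date on which all inclusion criteria, including elastography, are met. Other choices of time zero can be valid; one must be stated. Apply the existing eligibility criteria as of that date, and retain later decompensation, transplantation and death as outcomes or competing events.

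**If a waiver is not obtained.** State the survivor selection in Limitations, and do not use the retrospective part to estimate absolute risk.

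**Cost.** Protocol wording and a waiver request within an ethics application whose approval is still to be obtained. Nobody has been recruited, and no additional patients or procedures are needed. If records were extracted under a consent-only approval, recovering the excluded ones would take an amendment and a second extraction.

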## Results

At the time of manuscript submission, this protocol had not yet begun participant recruitment or data analysis. No participants had been recruited. The study did not receive external funding; therefore, no funding date is applicable. Data collection is projected to begin after institutional review board approval and ClinicalTrials.gov registration, with retrospective data extraction and prospective observational data collection expected to occur over approximately 24 months. The clinician-level randomized crossover simulation and pragmatic pilot implementation phases are expected to occur after model development and validation are completed. Data analysis will begin after completion of the relevant data collection phases. The main study findings are expected to be submitted for publication in summer 2029.

The integrated disease activity index is expected to show strong calibration with established prognostic scores and greater responsiveness to clinically meaningful changes, whereas the inclusion of PROs will provide a more comprehensive view of symptom burden. The predictive model is expected to achieve an AUROC of at least 0.85 for identifying CSPH and deliver a net reclassification improvement of 10% or more over Baveno VII criteria, reducing unnecessary endoscopies without compromising safety. Finally, the CDS prototype is expected to improve clinician adherence to guideline-concordant care pathways, reduce decision time, and achieve high usability and trust scores during the simulation and pilot phases.

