### Statistical Analysis

For the first aim, longitudinal PROs and biochemical markers will be analyzed using mixed-effects models to account for within-subject correlation and repeated measures over time. These models will assess the responsiveness of integrated symptom indexes to changes in biochemical progression or regression, whereas calibration of the AIm-PBC disease activity index will be evaluated against established risk scores such as UK-PBC and GLOBE using the calibration slope, intercept, and Brier score. Discrimination will be quantified through the AUROC, and visualizations of SHAP values will be examined to confirm clinical interpretability.

For the second aim, the predictive model for CSPH complications will be developed using gradient-boosted ensemble algorithms chosen for their robustness in handling heterogeneous data. Model performance will be assessed through the AUROC for discrimination and calibration plots for agreement between predicted and observed outcomes. Clinical utility will be evaluated using decision curve analysis and net reclassification improvement to determine whether the composite model offers meaningful improvement over existing criteria. Comparative analyses will use DeLong tests to assess differences in AUROC between models, and subgroup analyses will be conducted to evaluate fairness and consistency across patients with AIH overlap and MASH. Ablation studies will quantify the incremental value of individual predictors, particularly SSM, by systematically removing variables and observing changes in performance.

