## Discussion

### Principal Results

This protocol describes a multiphase study aimed at improving the management of PBC through an explainable AI framework. The anticipated results include a dynamic disease activity index that integrates biochemical, elastography, and patient-reported data, offering superior responsiveness and calibration compared to conventional monitoring. The predictive model is expected to achieve high discrimination for CSPH and outperform existing criteria, reducing unnecessary endoscopies while maintaining patient safety. Finally, the CDS prototype is designed to enhance clinician adherence to guideline-based care, improve decision accuracy, and reduce cognitive load, with usability and trust scores meeting or exceeding established benchmarks.

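### The expected 10% net reclassification improvement over Baveno VII does not support the safety wording attached to it, because an unsplit figure can hide a net loss among patients with CSPH

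*Protocol article*

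**What the plan says.** The Results section states what is expected of the second-aim model. It should "achieve an AUROC of at least 0.85 for identifying CSPH", and it should "deliver a net reclassification improvement of 10% or more over Baveno VII criteria, reducing unnecessary endoscopies without compromising safety". The NRI figure and the safety consequence thus stand in one sentence. Principal Results in the Discussion repeats the idea: the model is expected to outperform existing criteria, "reducing unnecessary endoscopies while maintaining patient safety".

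Statistical Analysis gives the NRI a working role in the second aim: "Clinical utility will be evaluated using decision curve analysis and net reclassification improvement to determine whether the composite model offers meaningful improvement over existing criteria". The other planned measures are AUROC with DeLong tests, calibration plots, subgroup analyses and ablation studies.

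The article does not divide the NRI into event and non-event parts. It states no sensitivity, negative predictive value or limit on unrecognised CSPH relative to Baveno VII. Sensitivity and specificity appear as model outcomes only in Table 1, for significant fibrosis.

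**The concern.** The model is meant to triage endoscopy referrals, so the error that bears on safety is a patient with CSPH placed in a lower risk class than Baveno VII would have given. The summed NRI counts that error, but lets it be offset by correct downward moves among patients without CSPH. One NRI figure can therefore describe a model that spares endoscopies at no cost to patients with CSPH, or one that spares them partly by moving such patients down.

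AUROC does not separate the two cases. It averages over all cut-offs and says nothing specific about performance at the lower triage threshold. If the article's expectations were met and reported in its own terms, the statement on fewer endoscopies could be well founded while the statement on safety rested on no figure that bears on it.

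**Working it through.** **Inputs from the protocol article.** Sample Size and Power Considerations gives "approximately 600 patients with PBC across participating sites" and a CSPH prevalence reported to "range from approximately 24% to 47% depending on disease stage and case mix". Results gives the NRI of at least 10% and the AUROC of at least 0.85.

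**The plan's own figure.** 600 × 0.24 = 144 and 600 × 0.47 = 282 patients with CSPH. Both agree with the stated range. Patients without CSPH number 600 − 144 = 456 and 600 − 282 = 318.

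**Formula.** NRI = [P(up | CSPH) − P(down | CSPH)] + [P(down | no CSPH) − P(up | no CSPH)]. With two risk classes this equals the change in sensitivity plus the change in specificity. Only the sum is fixed at 10%.

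**Splits that all give +10 points, if all 600 were analysed:**

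| CSPH / no CSPH (points) | Net moved down, 144 / 456 | Net moved down, 282 / 318 |
|---|---|---|
| 0 / +10 | 0 with CSPH, 45.6 without | 0 with CSPH, 31.8 without |
| −5 / +15 | 7.2 with CSPH, 68.4 without | 14.1 with CSPH, 47.7 without |
| −10 / +20 | 14.4 with CSPH, 91.2 without | 28.2 with CSPH, 63.6 without |

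In whole patients: −8/144 + 71/456 = 10.01%, and −15/282 + 49/318 = 10.09%.

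**Does the AUROC target exclude this?** The article gives no operating point for Baveno VII, so the values below are assumptions, with two risk classes and an equal-variance binormal ROC curve. AUROC 0.85 gives d′ = √2 × z(0.85) = 1.466, and specificity = Φ(d′ − z(sensitivity)).

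- Assume Baveno VII has sensitivity 0.90 and specificity 0.50. A model with AUROC 0.85 run at sensitivity 0.85 has specificity 0.666. NRI = −5.0 + 16.6 = +11.6 points.
- The same model run at sensitivity 0.90 has specificity 0.573. NRI = 0 + 7.3 = +7.3 points. Here the 10% is missed when sensitivity is held and reached when 5 points of it are given up.
- Five assumed Baveno VII points were tried, with sensitivity 0.90 or 0.95 and specificity 0.30 to 0.55, each with a 5-point loss of sensitivity. NRI ran from +6.6 to +22.3 points and passed 10 in four of the five; the exception was 0.90/0.55.

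**Would decision curve analysis show it?** The difference in net benefit, model minus Baveno VII, is Δsensitivity × prevalence + Δspecificity × (1 − prevalence) × w, with w = pt/(1 − pt) and pt the threshold probability. For −5/+15 it is zero where w = (0.05 × prevalence)/(0.15 × (1 − prevalence)).

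- At 24%: w = 0.012/0.114 = 0.105, so pt ≈ 9.5%.
- At 47%: w = 0.0235/0.0795 = 0.296, so pt ≈ 22.8%.

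Below these thresholds the model does worse than Baveno VII; above them it does better. Whether the loss shows depends on a threshold that the article does not name.

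**The case against.** The figures are expectations, not a decision rule. A reader might infer that a model less safe than Baveno VII could meet every target, be declared safe and so pass into the live pilot. The article does not support that. Outcomes and Statistical Analysis set no 10% or 0.85 success criterion, and Results places the pilot after development and validation without making it depend on either figure. This stands.

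A reader might also infer that safety is never examined. That goes too far. Decision curve analysis weighs missed cases against unnecessary referrals and could expose the loss at low thresholds, and Ethical Considerations provides for safety monitoring and suspension of the tool. But the curve analysis has no named threshold and no link to the safety statement, and the oversight responds to problems during use rather than comparing the model with Baveno VII.

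The splits are chosen for illustration and nothing in the article makes them likely. The counts use all 600 patients, whereas AI Model Development and Validation plans a held-out test set. With dual-threshold triage, a downward move need not take a patient below the lower threshold. All of this stands and limits the size of the point.

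Finally, an unseen analysis plan may split the NRI, and a journal article may properly leave that detail to it. The point does not rest on the missing detail. It rests on a single figure that the article states and on the conclusion it attaches to that figure.

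**Conclusion.** The point holds as a mismatch between a stated benchmark and the conclusion drawn from it. An NRI of 10% or more, read as the sum of its two components, sets no lower limit on the component in patients with CSPH, and an AUROC of 0.85 does not supply one. The additivity is certain on that reading, which is conventional; the article states no other.

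The illustrative size at −5/+15 is a net 7 of 144 to 14 of 282 patients with CSPH moved down if all 600 were analysed. The number would be smaller in the held-out set, and not all would be outright misses. The compatibility with AUROC 0.85 rests on assumed Baveno VII operating points and a binormal curve. None of this shows that the model will move more patients with CSPH down than Baveno VII does. It shows that the stated figures could not rule it out.

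**What to change.** - In Statistical Analysis (second aim) and Results, report the event and non-event NRI components separately, each with a CI, instead of relying on the summed 10%.
- At the lower triage threshold, locked before the test data are analysed, report the model's sensitivity for CSPH and the proportion with CSPH among patients classed low risk. Show both beside the Baveno VII values in the same test patients.
- Claim that safety is not compromised only if the event component and its CI support it. Otherwise remove the safety wording from Results and Principal Results.

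The cost is analysis and reporting wording. The change uses CSPH status and model output already planned for the second aim, so it needs no added procedure. Recruitment has not begun, so it can still be prespecified. The downside is real: the headline claim becomes harder to make, and the CI for the event component will be wide in the held-out set.
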